### Electroencephalograph Acquisition

While performing the experimental tasks, continuous electroencephalograph (EEG) activity is recorded using a NuAmps amplifier (Neuroscan Inc) located inside a soundproof, electrically shielded room. A 34-channel elasticized Quik-Cap with Ag/AgCl sintered electrodes (Neuroscan Inc) is used to record EEG data from scalp electrodes positioned according to the extended international 10-20 system (American Medical EEG Association, 1991). To control for the influence of ocular artifacts, vertical and horizontal electrooculograms are recorded in 2 bipolar channels. Eye blinks and vertical eye movements are monitored via electrodes located below and on the supraorbital ridge of the left eye. Horizontal artifacts are monitored via electrodes on the outer canthus of each eye. Linked mastoids (A1, A2) are used as reference, and participants are grounded to the AFz electrode. All data will be digitized using a NuAmps amplifier in continuous recording mode. Sampling rate will be 250 Hz, and all channels will be online band-pass filtered (0.1-70 Hz) and notch filtered (50 Hz) to eliminate power line artifacts. Analysis of the EEG recordings will be performed using the EEGLAB toolbox [76] and ERPLAB plugin for EEGLAB [77] both running under MATLAB environment (The MathWorks Inc). Continuous data will be filtered offline using a digital Butterworth filter (0.1-40 Hz; 12 dB per octave roll-off), an infinite impulse response filter that achieves a given filtering characteristic using less memory and fewer calculations than a similar finite impulse response filter. After filtering, data will be separated into baseline corrected and nonoverlapping epochs time-locked to the target onset (in both Stroop and oddball tasks) ranging from 200 ms before to 1000 ms after the onset of the target with the prestimulus interval (200 ms) as baseline period. Epochs containing high amplitude/frequency and muscle or other irregular artifacts will be removed by visual inspection. Only artifact-free epochs from correct trials will be selected for averaging. The existence of blinks and other ocular movements will not be a criterion for epoch rejection. This kind of artifact will be eliminated using Infomax Independent Component Analysis (ICA) decomposition [78-82]. We will use the default extended-mode *runica* training parameters [83], an extension of the original algorithm [78]. This extended mode allows a wider range of source signals (both super- and sub-Gaussian) while maintaining simplicity. Stopping weight change will be set to 1e–7. This rather conservative criterion for stopping learning lengthens ICA training, enabling cleaner and more reliable decompositions, particularly with more than 33 channels and limited number of epochs. After submitting epochs to ICA decomposition, artifactual components will be removed by inspection of their scalp topography and spectral power [84,27].

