**Results:**

We have recruited participants, have conducted the training protocol and pretest assessments, and are currently conducting posttest evaluations. The study will conclude in the first semester of 2017. Data analysis will take place during 2017. The primary outcome is transfer of benefit from training to attention and working memory functions and the neural mechanisms underlying possible cognitive improvements.

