## Methods

### Overview of the Study Design

A 2-arm, parallel-design RCT [72] was designed to evaluate the effectiveness of video game training to promote cognitive and brain health in older adults. Figure 1 shows the Consolidated Standards of Reporting Trials flow diagram of the study. This RCT is being conducted in Madrid, Spain, with an allocation ratio of 1:1 to evaluate the influence of training with nonaction video games on attention and memory functions. The design was a single-blind design. Eligible participants were randomized using a computer algorithm into intervention (cognitive nonaction video game training) or active control (life-simulation games) groups. Researchers were not blind to treatment allocation. The Universidad Nacional de Educación a Distancia (UNED) Institutional Review Board approved the study protocol. All participants provided written informed consent.

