### Participants

Participants were randomly assigned to 1 of the 2 parallel groups, either the intervention video game training group or the active control group (see Figure 1). The pretest, posttest, and 6-month follow-up assessments are conducted at the UNED Department of Basic Psychology II by one of the authors with the assistence of other members of the group. The training sessions were carried out at the UNED Associate Center, Escuelas Pías, Madrid, and lasted 8 to 10 weeks. A total of 138 participants were recruited from flyers, advertisements, by word of mouth, and from UNED’s special program for the elderly screened for eligibility. Finally, 75 older adults (age range 55 to 84 years) met the requirements for participation in the study and signed the consent form and were randomly assigned to the experimental or the active control groups before carrying out the laboratory tasks. The 2 groups do not differ significantly in age, years of education, global cognition, depression, memory, or verbal abilities.

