##### Corsi Blocks

The original task [106] consists of a set of 9 identical blocks (3 x 3 x 3 cm) irregularly positioned on a wooden board (23 x 28 cm). The participant is required to point to the blocks in their presentation order. The length of the block sequences increases until recall is no longer correct. Numerous variations have been employed. Here, we use a computerized version with 4 difficulty levels (2, 3, 4, and 5 cubes) with 10 trials per level. The task consists of reproducing the pattern of cubes just presented on the computer screen by writing down the order in which the cubes appeared on a response sheet. The score is derived from the number of sequences reproduced correctly divided by the total number of sequences in the corresponding level (correct/total sequences).

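### EEG epochs and ICA components are removed by inspection in a trial whose researchers are declared unblinded, and no masking is stated for that step, which leaves the ERP outcomes open to expectation bias of unknown size.

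*Protocol article*

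**What the plan says.** **Blinding.** Under Overview of the Study Design: "The design was a single-blind design", followed by "Researchers were not blind to treatment allocation". No exception is made for EEG processing. Under Participants, the three assessments are run "by one of the authors with the assistence of other members of the group", and randomization took place before the laboratory tasks. Even the pretest recordings therefore belong to people whose arm was already assigned.

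**Cleaning.** Electroencephalograph Acquisition describes two successive judgement steps. The first is "Epochs containing high amplitude/frequency and muscle or other irregular artifacts will be removed by visual inspection". The second, after the ICA decomposition, is that "artifactual components will be removed by inspection of their scalp topography and spectral power". Between them stands a partly objective rule: "Only artifact-free epochs from correct trials will be selected for averaging". Blinks and eye movements are not grounds for rejecting an epoch.

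**Status of the ERP results.** The abstract's Results paragraph says: "The primary outcome is transfer of benefit from training to attention and working memory functions and the neural mechanisms underlying possible cognitive improvements". The heading over the oddball and Stroop tasks within Primary Outcomes covers electrophysiological as well as behavioral results. Objectives and Hypotheses and the Oddball Task section predict better RON and P300 in the trained group. The latter expects no such pattern in the active controls.

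**The concern.** ERP amplitude is an average over the epochs that survive cleaning, after the chosen components have been subtracted. Whoever decides which epochs and components go has some influence on the result. If that person knows the arm and the session, and expects improvement in one arm at posttest, small unintended differences in strictness can produce the very interaction that the trial predicts.

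This goes beyond a detail left to a fuller document. The article gives the filter roll-off, the epoch window, the baseline and even the ICA stopping value, and within that detail it fixes removal by eye. Separately, it declares the researchers unblinded. The weakness lies in the combination of two stated choices.

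It also matters for this trial's purpose. The active control group and the expectation ratings are there so that a training effect cannot be put down to participants' expectations. The expectations of those who process the data have no stated safeguard.

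**Working it through.** The plan states no figure on this point, so there is none to reproduce. The check has a textual part and an illustration of sensitivity.

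**1. The text side by side**

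| Question | What the article gives |
|---|---|
| Are researchers masked to arm? | No, stated generally (Overview of the Study Design) |
| Is epoch rejection rule-based? | No, visual, without an amplitude or frequency limit |
| Is component rejection rule-based? | No, inspection of topography and spectrum, without a numeric rule |
| Coded files, independent processor or second rater? | None stated |
| Is a direction predicted? | Yes, RON and P300 in the trained group only |
| Is cleaning still ahead? | Abstract: posttests under way, data analysis during 2017 |

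**2. Sensitivity of the pre-post change contrast**

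Inputs from the article (Sample Size, Results):
- posttest completers: 38 − 8 = 30 and 37 − 12 = 25
- alpha 0.05

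Assumed, because the article does not give them:
- a two-sided test
- a pre-post correlation of 0.6
- a spurious shift b, in units of the outcome SD, affecting one arm at posttest only

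The planned analysis is a group × session ANOVA over three time points. The pre-post part of that interaction is the difference between arms in mean change:

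- SE of a single-time comparison: √(1/30 + 1/25) = 0.271
- SE of the change contrast: 0.271 × √(2 × (1 − 0.6)) = 0.271 × 0.894 = 0.242
- Type I error: P(|Z + b/SE| > 1.96)

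For b = 0.2: b/SE = 0.2/0.242 = 0.826. The upper tail is P(Z > 1.134) = 0.128 and the lower tail is P(Z < −2.786) = 0.003. The sum is 0.131.

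| Spurious shift b | correlation 0.5 (SE 0.271) | correlation 0.6 (SE 0.242) | correlation 0.7 (SE 0.210) |
|---|---|---|---|
| 0 | 5.0% | 5.0% | 5.0% |
| 0.1 SD | 6.6% | 7.0% | 7.6% |
| 0.2 SD | 11.4% | 13.1% | 15.9% |
| 0.3 SD | 19.8% | 23.6% | 29.9% |

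An exact noncentral t on 53 degrees of freedom gives 12.8% in place of 13.1%.

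A shift that is the same at pretest and posttest cancels in this contrast, as does one that is the same in both arms. Only a shift that differs by arm and session together counts.

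**3. How uneven would cleaning have to be?**

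A simulation of 4,000 null trials used assumed values throughout: 40 epochs per person, single-trial SD 10 µV, and between-person SD of change 3 µV. With 20% of epochs removed, type I error was:
- 0.046 when removals were random
- 0.164 when a quarter of the removals in the experimental posttest files came from the lowest amplitudes (spurious difference about 1.0 µV)
- 0.050 with coded files

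The last result follows from the set-up, in which coding means that selection cannot depend on arm. With 10% removed and the same quarter tilted, the figure was 0.085. The article gives no epoch count, rejection rate or ERP SD, so these results show only the direction and how steep the effect could be.

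**The case against.** **The article does not say who cleans the files.** The sentences are passive, and the unblinded statement is a general one. A reader might infer that the person deleting epochs is known to have seen the allocation. The documents do not establish that. It is the plain reading of two sections taken together, and a lab procedure could provide masking that a condensed article leaves out. This limits the wording to saying that no masking is stated. It does not remove the point, because the only statement on researcher blinding is negative and without exception.

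**Discretion is bounded.** Averaging is limited to correct trials, ocular artifacts do not lead to epoch rejection, and the filters, window, baseline and ICA stopping value are fixed. Components are judged on topography and spectrum, not on P300 or RON amplitude. All of this stands and narrows the scope for bias, but both removal decisions remain matters of judgement.

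**The status of the ERP results is mixed.** The closing summary of primary measures, under Assessing Working Memory Updating, names performance on four tasks, and General Procedure presents the ERPs as exploring mechanisms. Against that stand the abstract and the Primary Outcomes headings.

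**The percentages are hypothetical.** That is correct. No section supplies a shift or a correlation, so the figures are not estimates of this trial's error rate.

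**The Corsi task.** A reader might think its response sheets are exposed in the same way. They are not. The participant responds "by writing down the order in which the cubes appeared on a response sheet", and the score is the number of correct sequences over the total at each level, which leaves a scorer little room beyond an illegible entry.

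**Conclusion.** The concern holds as a risk of bias, not as bias shown. The stated plan combines unblinded researchers with two cleaning steps by eye, for directional ERP outcomes that the article places within its primary outcome, and no masking is stated. A false group × session interaction could arise this way.

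The size is unknown. On the assumptions shown, a differential shift of 0.2 SD takes the type I error of the pre-post contrast from 5% to about 13%; over shifts of 0.1 to 0.3 SD at correlation 0.6 the range is about 7% to 24%.

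A reader might also infer that coding the files would make the ERP comparison free of bias. It would not. It acts only on offline processing. It leaves the testing sessions run by unblinded staff, and the unequal losses of 8/38 = 21% v 12/37 = 32%, as they are.

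**What to change.** Add to Electroencephalograph Acquisition, in wording such as: *Before epoch and component rejection, EEG files are renamed with random codes that hide participant and arm, and also session where timing allows. Rejected epochs and components are saved. The key is held by a team member who does not clean the files and is released only after the ERP averages are locked.* If masking of this kind is already in place, stating it is enough.

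The cost is a modest amount of file handling and one person kept apart from the cleaning. No participant procedure changes. If session is masked too, cleaning has to wait until the later recordings are in; masking participant and arm alone avoids most of that delay. Since the abstract places data analysis in 2017, after the article was written, the change was still feasible then.

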
### General Procedure

Participants in the study were randomly assigned to the cognitive nonaction video game training group or the noncognitive game training active control group. The introduction of an active control group is necessary to avoid placebo effects [54]. Based on the results of our meta-analytic study [61], we use training regimes that are not too long to avoid loss of motivation, and simple, nonaction games that appeal more to elders. According to the temporal discount hypothesis [85], future rewards are less valuable than inmediate rewards. In each session, the trainees play 10 nonaction video games from Lumosity, described below.

The main question examined in our study is whether group (experimental group, active control group) interacts with testing session (pretest, posttest, and follow-up) with regard to performance on a series of cognitive tasks. At least 2 measures for each cognitive domain are acquired to examine transfer of training to untrained tasks demanding attention and working memory. We selected these cognitive domains because these functions deteriorate with aging and tax functions that are critical for independent living. To explore the underlying neural mechanisms of successful transfer of training gains to attentional mechanisms (alert, distraction, and inhibitory effects) and executive control (spatial working memory), electrophysiological data (ERPs) are recorded at pretraining (T1), posttraining (T2), and 6-month follow-up (T3).

All the methodological designs of the primary outcome measures have been constructed using the rules of counterbalancing and stimulus rotation. Response keys are counterbalanced across conditions. The computerized tasks have been programmed using E-Prime 2.0 (Psychology Software Tools Inc). All the statistical analyses of the behavioral results will be performed using SPSS (IBM Corp) and results will be considered significant at *P*<.05, with Bonferroni-corrected post hoc tests performed as appropriate. Continuous EEG activity are recorded in our laboratory with thin electrodes from 34 scalp sites using a NuAmps amplifier as mentioned before.

After randomization and initial assessment (baseline), participants were invited to attend the University Center of Escuelas Pias in Madrid to perform the training sessions in small groups. Trained and active control groups followed 16 training sessions carried out on different hours and days that lasted approximately 10 to 12 weeks.

Table 1 presents a short summary of the video games played by the experimental (trained) group. During the training sessions, participants in the experimental group play 10 nonaction video games selected from Lumosity.

The active control group carried out 16 training sessions with The Sims and SimCity BuildIt. Table 2 presents a short summary of these video games.

**Table 1 table1:** Short description of the 10 video games played by the experimental group.

Game name	Trained function	Description
Tidal Treasures	Working memory	Player chooses objects and memorizes their choice.
Pinball Recall	Working memory	Player predicts a ball’s path.
Playing Koi	Divided attention	Player feeds fish and remembers which have already been fed.
Star Search	Selective attention	Player chooses the odd one out in a group of objects.
Lost in Migration	Selective attention	Player swipes in the direction the middle bird is facing in a flock of birds that appears on the screen.
Color Match	Response inhibition	Player compares one word's meaning to another word's color.
Disillusion	Task switching	Player matches tiles with different shapes, colors, or symbols.
Ebb and Flow	Task switching	Player swipes in the direction leaves are moving or pointing.
Highway Hazards	Information processing	Player races a car across the desert avoiding colliding with obstacles.
Speed Match	Information processing	Player determines whether a card appearing on the screen is the same as or different than the previous one.

**Table 2 table2:** Life simulation games from Electronic Arts Inc played by the active control group.

Game name	Trained function	Description
SimCity BuildIt	None	Life simulation game in which the player is the mayor of a city that he or she must expand.
The Sims	None	Life simulation game in which the player creates characters (The Sims) that live in a virtual world that is similar to the real one. The Sims work, build their own homes, develop relationships, etc.

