##### Stroop and Negative Priming Task

Cognitive processes that involve top-down control mechanisms decline with aging but more automatic processes do not [20,22]. The Stroop interference effect reflects the extra time needed to resolve the conflict generated by the irrelevant word meaning in the incongruent condition. One view is that suppression processes relying on executive control are engaged in preventing the irrelevant dimension from taking control of the response [97]. In this study, we investigate the effect of training older adults with nonaction video games on inhibition processing using both behavioral and electrophysiological responses. The task has been designed to assess training-related behavioral and neural changes in Stroop interference and in negative priming (NP). NP (a measure of distractor inhibition) and the standard Stroop effect are assessed in the same task. In the standard NP procedure, participants are presented with pairs of prime and probe displays containing 2 stimuli, the to-be-responded target and the to-be-ignored distractor. In the critical trials, participants must respond to a target that served as a distractor in the previous prime display (the ignored repetition condition). The common finding is that reaction times to targets in the ignored repetition condition are slower than in the control condition, in which the distractor in the prime display is not repeated as the target in the probe display [98-101]. The aim is to investigate whether training older adults improves control, effortful inhibition (Stoop interference), to a greater extent than automatic passive inhibition (NP). The experimental task uses ERPs in combination with the Stroop and NP before and after training to examine the neural correlates of inhibition [102]. Responses for the Stroop analysis will be coded as a function of the congruency between the color and the meaning of the stimulus. Congruent trials are those in which the color of the word coincides with the color in which it is presented. Incongruent trials are those in which the color word does not coincide with the color in which it is displayed. We will also code trials according to the congruency of the previous trial (N−1) in order to compute the NP effect for each trial. The design for the NP effect consists of Group (younger, older adults), Session (pretraining, posttraining, follow-up), and Type of intervention (experimental, active control) as between-participants factors and Repetition (ignored repetition and control) as within-participants factors. Responses for NP analyses will be coded as a function of the relationship between the color of the current target word and the color denoted by the word in the previous trial (distractor). Thus, the ignored repetition trials are those in which the word in the preceding trial denoted the color of the word of the current stimulus. Control trials are those in which both the target (color) and the distractor (word) in the current trial are different from the target and distractor in the previous trial. The ignored repetition condition is always an incongruent trial preceded by an incongruent trial. The aim is to investigate whether the Stroop interference effect in older adults decreases after training while NP does not change. An important addition to the behavioral measures will be the ERP recording while performing the task before and after training to investigate brain activity changes after training.

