##### Assessing Working Memory Updating

Transfer to working memory after training is assessed with the *n*-back task [107]. We use a computerized version of the task to assess memory updating. In this task, participants indicate whether each visual stimulus in a list matches a stimulus that occurred 1, 2, or 3 stimuli back by pressing a response key with their right hand (counterbalancing index and middle fingers to respond “yes” and “no”).

In sum, the primary outcome measures of this RCT are better performance at posttest than at pretest on a series of tasks: (1) Stroop-negative priming task, (b) oddball task, (3) *n*-back task, and (4) Corsi blocks.

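### Two games played only by the experimental arm use nearly the same rules as Stroop interference and 1-back, yet the protocol counts both as transfer to tasks outside the training

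*Protocol article*

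**What the plan says.** Under General Procedure, the experimental arm plays all ten Lumosity games in each session. The abstract gives sixteen one-hour sessions. Two of the ten entries in Table 1 matter here:

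- Color Match, listed as training response inhibition: "Player compares one word's meaning to another word's color".
- Speed Match, listed as training information processing: "Player determines whether a card appearing on the screen is the same as or different than the previous one".

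The active control arm plays The Sims and SimCity BuildIt, for which Table 2 lists no trained function.

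The primary outcome tasks, listed at the end of Assessing Working Memory Updating, are ("1) Stroop-negative priming task, (b) oddball task, (3) *n*-back task, and (4) Corsi blocks"). Two of them are defined as follows:

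- Stroop: "Responses for the Stroop analysis will be coded as a function of the congruency between the color and the meaning of the stimulus".
- n-back: "participants indicate whether each visual stimulus in a list matches a stimulus that occurred 1, 2, or 3 stimuli back".

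General Procedure gives their purpose: "At least 2 measures for each cognitive domain are acquired to examine transfer of training to untrained tasks demanding attention and working memory". The Results part of the abstract likewise frames the primary outcome as transfer of benefit. Under Objectives and Hypotheses, oddball and Stroop represent attention, and Corsi and n-back represent working memory. The article does not distinguish tasks whose rule is practised in training from tasks whose rule is not.

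**The concern.** The trial's main conclusion is meant to be that game training carries over to tasks that were not trained. It rests on the interaction between group and testing session. If one arm has rehearsed the rule of an outcome task for sixteen sessions and the other has not, rule-specific practice and genuine transfer predict the same interaction on that task. The active control equalises hours, engagement and social contact, but its games are not described as containing either rule, so it cannot separate the two explanations.

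The Stroop inference is the more exposed. The section on the Stroop and negative priming task asks whether interference falls after training while negative priming stays as it was, as a sign that effortful inhibition improves more than automatic inhibition. Rehearsing colour-word conflict could produce that pattern without any general gain in inhibition. ERP changes recorded during the Stroop task share the ambiguity.

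**Working it through.** The point is one of construct validity. The plan offers no figure to reproduce, so the check sets the game descriptions in Table 1 beside the definitions of the primary outcomes.

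| Primary outcome component | Rule of the outcome | Closest game in Table 1 | Overlap |
|---|---|---|---|
| Stroop interference | conflict between ink colour and word meaning | Color Match: meaning of one word against colour of another | close |
| Negative priming | slowing when the word just ignored names the current colour | Color Match, indirectly | weaker |
| 1-back | does this item match the one before it? | Speed Match: same as or different from the card before | close |
| 2- and 3-back | match to an item two or three back, which needs updating | Speed Match, indirectly | weaker |
| Oddball | distraction by a novel stimulus and return to the task | Star Search: pick the odd object out of a group | weaker, different rule |
| Corsi blocks | reproduce the order of a spatial sequence | Tidal Treasures and Pinball Recall, labelled working memory | same domain, different rule |

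**Count.** Close overlap occurs in two components, one in each of two of the four primary tasks. By domain, attention has two tasks, of which Stroop is affected in its interference component. Working memory has two tasks, of which n-back is affected at one of its three loads. Each domain keeps one task (oddball, Corsi) with no game that uses the same rule.

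**Exposure, as an illustration only.** If the ten games shared the hour equally, each game would take 60 / 10 = 6 minutes per session, and 16 × 6 = 96 minutes over the programme, against none described for the control arm. The article does not give time per game, so the 96 minutes is an assumption and nothing below depends on it. Because all ten games are played in each session, exposure in the experimental arm is above zero however the hour was divided.

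**Inference.** Suppose the arms differ at posttest on Stroop interference and 1-back, and on nothing else. Rule practice predicts this, and so does transfer. The article gives no rule for telling them apart, and its framing would report the result as transfer. If the difference also appears on oddball, Corsi or the higher n-back loads, rule practice is a much weaker explanation.

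**The case against.** Several objections narrow the point, and most of them stand.

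- *The games are not the tests.* Training was on a tablet. The outcomes are separate E-Prime tasks with counterbalanced keys and rotated stimuli, and Color Match uses two words where the Stroop task uses one. A reader might infer that participants rehearsed the outcome tests themselves and that gains on them mean nothing. The article does not support that. It supports close similarity of rule, read from one-line game descriptions.
- *Speed Match is listed under information processing, not working memory.* True, but the label does not alter the rule that the player follows.
- *Half of the primary outcomes are not lost.* A reader might count Stroop and n-back as wholly compromised. Negative priming and two of the three n-back loads are touched only indirectly, so that count is too high.
- *Two measures per domain already give protection.* They do keep transfer testable in both domains. However, all four tasks are listed on an equal footing, so nothing prevents a transfer claim that rests on the affected components alone.
- *Earlier results were not automatic gains.* The overview of spatial working memory acknowledges that several nonaction games resemble working memory tasks, and says so while discussing training that proved ineffective. A practice gain is therefore possible rather than certain. The difficulty lies in how a gain, if found, would be read.
- *Near- and far-transfer labels can wait for a fuller plan.* Detail can. But the choice of games and the stated meaning of the primary outcomes are fixed in this article, and they do not fit together.
- *Any split is partly a matter of judgement.* This stands. Star Search and the two working memory games have some kinship with oddball and Corsi, and 1-back practice may help at higher loads. The split should be presented as a graded judgement.

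**Conclusion.** The point holds in a limited form. Color Match and Speed Match, played only in the experimental arm, use nearly the same rules as Stroop interference and 1-back. The protocol nevertheless offers both as evidence of transfer to tasks outside the training. A gain confined to them would not distinguish transfer from rule-specific practice.

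A reader might go further and infer that the randomised comparison is biased. It is not: the contrast between arms validly estimates the effect of the training package on every outcome, including these two. Only the reading of that effect as transfer is in question.

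The conclusion assumes that the short descriptions in Table 1 represent the games fairly, and that the control games contain neither rule, as Table 2 implies. It does not depend on the time spent on each game. The matter deserves correction before analysis because it changes what the trial may conclude, although the data remain usable as collected.

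**What to change.** Before the data are analysed, issue a dated amendment that:

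1. labels Stroop interference, with its ERP measures, and 1-back as trained-paradigm (near-transfer) outcomes;
2. requires n-back results to be reported separately by load;
3. states that a claim of transfer to tasks outside the training needs a gain on oddball, Corsi or 2-/3-back;
4. reports negative priming separately;
5. acknowledges the weaker overlap of other games, such as Star Search with oddball and the working memory games with Corsi.

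No new participants, assessments or changes to training are needed. Because training is complete, posttests are in progress and the researchers are not blinded, the amendment should give its reason and say which outcome data, if any, had been examined by its date. The scientific cost is that a gain on Stroop interference or 1-back alone would no longer support the transfer claim. Such a gain would still be reported, under the near-transfer label.
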